### Standard of care control condition

For Stage 1 (PrEP linkage/uptake), the SOC condition consists of the provision of resources including information about oral and injectable PrEP (what they are, how they work, their efficacy), how to pay for PrEP with or without insurance, and a list of local resources for mental and sexual health, primary care, sexual assault, domestic violence, substance use, and HIV/STI care and prevention. Irrespective of the study condition, if they attend a PrEP appointment, participants can be prescribed PrEP at the discretion and following the protocol of the prescribing clinician.

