For mediation analyses, path analysis will be conducted using structural equation modeling (SEM) to determine whether the effect of the intervention on uptake and/or adherence was through the hypothesized mediators (e.g., increased PrEP knowledge, increased problem-solving skills to take PrEP, increased self-efficacy for PrEP adherence). SEM allows for the simultaneous estimation of total, direct, mediated, and indirect effects of a causal variable (i.e., the intervention) on the outcome (i.e., adherence) through a set of mediator variables [31]. SEM can handle outcomes and mediators with a variety of distributions (including Gaussian, Poisson, and Binomial). Inferences for indirect effects will be estimated using bootstrapped confidence intervals [32]. For effect modification (moderation) analyses, we will add interaction terms one by one for the intervention condition and the potential moderators (e.g., race, substance use at baseline, psychosocial factors; see Measures). Significant or large interaction terms suggest that intervention effects differ by subgroups of the moderators.

#### Aim 3

For the cost-effectiveness analysis, the costs of providing this intervention relative to the SOC arm will be estimated based on detailed records of resources required to implement the intervention from an organizational perspective, including the average personnel cost per participant for each intervention arm. The lifetime treatment cost of an HIV infection will be used as a conservative threshold value for the cost of averting one infection. The intervention will then be deemed cost-saving if it costs less than this threshold.

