## Discussion

The “PrEPare for Work” intervention is the first theory-based PrEP uptake and adherence intervention for MSWs, who are among the most marginalized, at-risk and understudied populations in the U.S. “PrEPare for Work” was informed, developed, and refined through formative community-based research that involved MSWs at each stage to ensure study implementation and design, as well as intervention content addresses and honors their lived contextual realities and that those who are most in need benefit from this transformative biomedical HIV prevention modality. For example, as many MSWs are not publicly open about their involvement in sex work or are afraid of legal ramifications, our recruitment materials use less explicit language to highlight paid research opportunities about men and sexual health.

The integration of text messaging technology to support adherence, which we found to be highly acceptable and feasible in the pilot RCT of this intervention [17], has been used successfully with other populations [33, 34] but has not been used previously with MSWs — given the broad use of mobile phones to connect with both clients and personal networks, this component has unique promise. Furthermore, the design of “PrEPare for Work” allows us to efficiently test both the PrEP initiation and PrEP adherence components of the intervention, which aligns with real-world clinical settings — firstly, PrEP is provided only within usual clinical care; and secondly, if a person is not ready nor feeling empowered to initiate PrEP, an adherence intervention is not responsive nor an appropriate use of resources. Thus, this study is testing an intervention within a real-world context and hence may provide evidence of a sustainable and scalable intervention, which could be adapted for other sex worker populations in the US and potentially globally and among other groups with shared risk factors. Ultimately, if efficacious, this intervention could be integrated within existing healthcare systems and community harm reduction organizations.

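### Aim 3 sets delivery cost to the organisation against a health-care saving, so its rule can report 'cost-saving' while total health-care spending rises

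*Protocol article*

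**What the plan says.** All of this is in the protocol article, under Statistical analyses, Aim 3, unless another section is named.

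- **Cost side.** What is estimated is "the costs of providing this intervention relative to the SOC arm", from records of "resources required to implement the intervention from an organizational perspective, including the average personnel cost per participant for each intervention arm".
- **Threshold.** "The lifetime treatment cost of an HIV infection will be used as a conservative threshold value for the cost of averting one infection". No amount is given.
- **Rule.** "The intervention will then be deemed cost-saving if it costs less than this threshold".

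Three other places show where PrEP itself sits.

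- The Discussion says that "PrEP is provided only within usual clinical care".
- Standard of care control condition says that, whatever the arm, "participants can be prescribed PrEP at the discretion and following the protocol of the prescribing clinician". The material handed to controls explains "how to pay for PrEP with or without insurance".
- Co-primary outcome measures has staff contact outside PrEP providers and pharmacies to confirm visits and fills.

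**The concern.** The two sides of the rule are drawn from different accounts. The saving is HIV treatment that the health-care system no longer has to provide. The cost is what an organisation spends to run case management, counselling and text messages. Between them lies the step that produces the saving: more people taking PrEP, with the drug, clinic visits and laboratory tests that this brings. Those are health-care costs too, but the delivering organisation does not bear them, so an organisational perspective does not pick them up.

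In Stage 1 this cost is the mechanism of the intervention, since infections are averted there only through additional PrEP use. The better Stage 1 works, the larger the uncounted item.

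At stake is the wording of Aim 3's conclusion. Cost-saving is a stronger claim than cost-effective: it says that total spending falls. The Discussion foresees use within existing health-care systems, which may be the ones paying for the PrEP.

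**Working it through.** The article states no cost result, so there is no figure to reproduce. The check is on the logic of the rule, followed by an illustration.

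**1. The rule in symbols.** Per participant, relative to standard of care, let D be the extra delivery cost, P the extra PrEP-related cost and a the infections averted. Let T be the lifetime treatment cost of one infection. The threshold is per infection, so the sensible reading of the rule is cost per infection averted.

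- Rule as stated: D/a < T, that is, D < aT.
- Net saving in health-care spending: (D + P)/a < T, that is, D + P < aT.
- The two disagree whenever D < aT < D + P. This range exists for any P above zero.

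**2. Is P above zero in Stage 1?** The article's own figures imply that it is.

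- Sample size calculations: 63 completers per arm with 20% attrition, so 63/0.8 = 78.75 per arm and 157.5 initiators in total. Out of 500 this is 31.5%.
- Background: in the pilot, uptake steps were two to three times more likely with case management.
- With equal arms and ratio r, control uptake s satisfies s(1 + r)/2 = 0.315.
- r = 2: s = 0.63/3 = 21%, against 42%, a difference of 21 points.
- r = 3: s = 0.63/4 = 15.75%, against 47.25%, a difference of 31.5 points.

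So the planning figures imply about 21 to 32 extra PrEP starters per 100 participants.

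**3. How much PrEP per infection averted (new users only).** Person-years of PrEP per infection averted = 1/(incidence × effectiveness). Both inputs are assumptions.

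| Incidence per 100 person-years | Effectiveness | PrEP person-years per infection averted | Annual PrEP cost at which savings vanish even if D = 0 |
|---|---|---|---|
| 1 | 0.5 | 200 | 0.5% of T |
| 3 | 0.7 | 47.6 | 2.1% of T |
| 5 | 0.9 | 22.2 | 4.5% of T |
| 8 | 0.9 | 13.9 | 7.2% of T |

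**4. One worked example.** All inputs are assumed: T = 400,000, incidence 3 per 100, effectiveness 0.7, uptake up 25 points for one year, D = 1,000.

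- a = 0.25 × 0.03 × 0.7 = 0.00525, and aT = 2,100.
- Rule: 1,000/0.00525 = 190,476, below T, so cost-saving.
- PrEP at 8,000 a year: P = 0.25 × 8,000 = 2,000; (1,000 + 2,000)/0.00525 = 571,429, above T, so not cost-saving.
- PrEP at 2,000 a year: P = 500; 1,500/0.00525 = 285,714, below T, so both versions agree.
- The label changes at an annual PrEP cost of (2,100 − 1,000)/0.25 = 4,400.

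**5. A wider grid.** With T, effectiveness and the uptake difference as in step 4, take incidence 1, 3 and 5 per 100, annual PrEP cost 500, 2,000, 8,000 and 20,000, and D of 250, 500, 1,000 and 2,000. This gives 3 × 4 × 4 = 48 combinations. The rule says cost-saving and the full-cost version does not in 6 + 10 + 5 = 21 of them, taking the three incidences in order. The two agree in the other 27. This describes the assumed grid and is not a probability.

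**6. Onward infections.** If each infection averted also prevents onward ones, so that aT is multiplied by m, the 8,000 case in step 4 breaks even at m = 3,000/2,100 = 1.43. An allowance of 0.43 onward infections per infection averted would therefore remove the disagreement in that case.

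**The case against.** The strongest reply is that the exclusion of PrEP is inferred. Personnel cost is named as an included item, which does not make the list exhaustive, and Aim 3 is a short paragraph in an article that condenses a fuller plan. A reader might conclude that PrEP costs are definitely left out; the article does not say so. What stands is narrower: the perspective is stated, PrEP is placed outside the delivering organisation, and a rule applied on that perspective does not reach it. A full plan that counts PrEP would answer the point.

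A reader might also infer that calling the threshold conservative is an error. The text does not support that. The word describes the threshold, and one built on treatment cost alone gives no credit for health gained, so the description is defensible. The narrow cost side is a separate matter.

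Other objections also stand in part.

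- Onward infections averted would work in the intervention's favour, so the net direction cannot be read from the documents. The Background itself cites modelling of benefit beyond male sex workers.
- Every monetary and epidemiological input above is assumed.
- The person-years formula describes new users against no PrEP. It does not fit Stage 2, which re-randomises people who have already started; extra spending there comes only through longer persistence or more refills.
- Aim 3 is conditional on efficacy and touches no primary outcome or sample size.

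These limit the size of the point. They do not remove the mismatch between the two sides of the rule.

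**Conclusion.** The point holds as a fault in a stated decision rule. Followed as written, the rule credits an averted health-care cost on a perspective that does not cover the health-care cost of averting it, and it gives the wrong label whenever delivery cost < averted treatment cost < delivery plus induced PrEP cost.

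A reader might go further and infer that the trial will report a false saving. The documents do not support that, because they give no PrEP price, incidence, effectiveness, onward transmission or threshold amount. In the assumed example the label reverses at 8,000 a year for PrEP and stands at 2,000. The issue bears mainly on Stage 1 and less on Stage 2. It should be corrected before Aim 3 is analysed; it does not affect the primary comparisons.

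**What to change.** Choose one of two routes and state it before the analysis.

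1. **Keep the cost-saving question.** Use one health-care-sector perspective on both sides and state the comparison as incremental cost per infection averted. Add incremental PrEP drug, visit and laboratory costs to delivery cost, and reserve 'cost-saving' for a net incremental cost (delivery plus PrEP minus averted treatment) below zero. State whether onward infections are counted. Take PrEP use from pharmacy and medical records where available. These will be incomplete for Stage 1: the medical release is obtained at Stage 2 baseline, and non-initiators have their last assessment at two months. Later PrEP starts therefore need a stated modelling assumption with a sensitivity range.
2. **Keep the organisational perspective.** Report delivery cost per infection averted and drop the cost-saving label.

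Neither route changes trial conduct. The first needs modest analysis work and outside unit costs, and is likely to give a less favourable and more uncertain result. The second costs a change of wording and gives up the stronger claim.

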### Sample size calculations

The primary power analysis is based on the acute PrEP adherence outcome (differences between the intervention and control conditions from our “PrEPare for Work” pilot RCT), which demonstrated a meaningful but non-significant difference in PrEP adherence between the intervention and control groups from baseline to follow-up (effect size: 0.54) [17]. Therefore, the present study is powered to detect an effect size of d = 0.54 using a two-sided alpha = 0.05. Group sizes of 63 completers per arm (experimental intervention and the standard of care comparison), which assume 20% attrition in Stage 2, result in greater than 80% power in adherence at four months in a pair-wise comparison. Assuming similar rates of uptake and attrition to the pilot study, 250 individuals per arm are required for randomization.

### Data management, safety and monitoring

All survey data is inputted directly into REDCap, a HIPAA-compliant, comprehensive data management system. Hard and soft-copy participant data is identified by an ID number only, and a link between names and ID numbers is kept separately in a password-protected file. Likewise, name-based files are stored separately from survey data. Soft copy data is stored on study-specific secure and password-protected network drive folders, accessible only to study staff. Hard copy data is stored in locked cabinets within restricted and secure areas at study sites.

All study staff are trained in confidentiality and have signed confidentiality agreements. Study staff have been trained in ethical human subject research practices to minimize participant risk. The investigators report unanticipated problems, safety monitors’ reports, and adverse events to the University of California, Los Angeles IRB, per IRB policies. Any protocol modifications will be reported to and approved by the UCLA IRB.

Given that this is a behavioral intervention with minimal risk, the study has no stopping rules, and interim analyses are not conducted. An independent Data Safety Monitoring Board has been assembled and reviews study progress, including safety concerns and adverse events, twice annually. All reports are shared with the IRB and funder at least annually.

### Dissemination plan

In addition to reporting on clinicaltrials.gov, findings from this study will be disseminated via peer-reviewed publications and conference abstracts/presentations. Moreover, presentations at community organizations, including our partner SSP sites, and government entities (e.g., local public health departments, CDC) will be conducted. We will also create easy-to-read infographics to share via social media and our research group website(s).

## Discussion

The “PrEPare for Work” intervention is the first theory-based PrEP uptake and adherence intervention for MSWs, who are among the most marginalized, at-risk and understudied populations in the U.S. “PrEPare for Work” was informed, developed, and refined through formative community-based research that involved MSWs at each stage to ensure study implementation and design, as well as intervention content addresses and honors their lived contextual realities and that those who are most in need benefit from this transformative biomedical HIV prevention modality. For example, as many MSWs are not publicly open about their involvement in sex work or are afraid of legal ramifications, our recruitment materials use less explicit language to highlight paid research opportunities about men and sexual health.

The integration of text messaging technology to support adherence, which we found to be highly acceptable and feasible in the pilot RCT of this intervention [17], has been used successfully with other populations [33, 34] but has not been used previously with MSWs — given the broad use of mobile phones to connect with both clients and personal networks, this component has unique promise. Furthermore, the design of “PrEPare for Work” allows us to efficiently test both the PrEP initiation and PrEP adherence components of the intervention, which aligns with real-world clinical settings — firstly, PrEP is provided only within usual clinical care; and secondly, if a person is not ready nor feeling empowered to initiate PrEP, an adherence intervention is not responsive nor an appropriate use of resources. Thus, this study is testing an intervention within a real-world context and hence may provide evidence of a sustainable and scalable intervention, which could be adapted for other sex worker populations in the US and potentially globally and among other groups with shared risk factors. Ultimately, if efficacious, this intervention could be integrated within existing healthcare systems and community harm reduction organizations.

There are potential limitations to the proposed project. Firstly, the RCT may not be powered to determine intervention efficacy for our secondary outcome of PrEP persistence; however, findings may still help inform subsequent research. Secondly, the formative research and pilot study was comprised of primarily street-based sex workers in the U.S. Northeast [11, 17, 25, 35]. Given that the present study aims to broaden its sample across geography and sex work type, its content may need to be slightly adapted to ensure relevance across diverse potential participants. Importantly, our mediation and moderation analyses will provide more insight into those mechanisms of action and subgroup differences, which can inform future broadening in scope.

In sum, based on formative work and community collaboration, we developed the theory-informed, multi-component “PrEPare for Work” intervention targeting PrEP knowledge, motivation, self-efficacy, behavioral skills, and structural barriers to access among MSWs at risk of HIV acquisition. Importantly, this RCT plans to enroll MSWs in diverse geographic areas and with diverse sex work and lived experiences, providing insight into the generalizability of this intervention. If efficacious, findings could inform the dissemination of “PrEPare for Work” to community-based and clinical settings throughout the U.S.

## Data Availability

Reasonable requests to access study data will be considered by the corresponding authors(s), and upon completion of planned study outcome analyses, raw data will be freely available to any scientist wishing to use them for non-commercial purposes, without breaching patient confidentiality, per journal guidelines.
